## Abstract

**Background:**

The latest meta-analysis demonstrated that acupuncture improves pregnancy rates among women undergoing *in vitro* fertilization-embryo transfer (IVF-ET), and surface acupoint stimulation, such as transcutaneous electrical acupoint stimulation (TEAS), may have the same or better potential.

**Methods/Design:**

To explore the effect of TEAS on the clinical pregnancy rate (CPR) and live birth rate (LBR) compared with real acupuncture and controls in women undergoing IVF, a multicenter, randomized controlled trial will be conducted. The inclusion criteria are the following: infertile women <40 years of age undergoing a fresh IVF or intracytoplasmic sperm injection cycle, and the study will be restricted to women with the potential for a lower success rate as defined by two or more previous unsuccessful ETs (fresh or frozen). Those who have severe illnesses possibly precluding IVF or pregnancy, have FSH levels greater than 20 IU/L, received donor eggs, had been previously randomized for this study or had undergone acupuncture (in any modality) as infertility treatment will be excluded. The subjects will be randomly assigned to the TEAS group (IVF + TEAS), the electro-acupuncture (EA) group (IVF + EA), or the control group (only IVF). A total sample size of 2,220 women is required to detect differences in CPR among the three groups. TEAS or EA treatments will start once every two or three days from day 3 of menstruation in the ovarian stimulation cycle until the day of ET. The parameters of TEAS or EA will be the following: a frequency of 2/100 Hz, a moderate electrical current of 3 to 5 mA for TEAS and 0.8 to 1.0 mA for EA. The primary outcome is CPR. Secondary outcomes are LBR, the number of oocytes aspirated and the total gonadotropin dose used in the stimulation cycle.

**Discussion:**

This study will provide significant evidence for using a new method (TEAS) in IVF.

**Trial registration:**

ClinicalTrials.govID: NCT01608048 (05/24/2012).

## Background

*In vitro* fertilization-embryo transfer (IVF-ET) is the most successful infertility treatment, and for many people, this treatment represents the last possibility for pregnancy. However, the average IVF success rate per cycle using fresh, nondonor oocytes is still not satisfactory [1]. The majority of IVF cycles do not result in pregnancy. Although techniques such as controlled ovarian hyperstimulation (COH), *in vitro* fertilization, and embryo culture and transfer have greatly improved, certain patients are not successfully treated, even after several ETs.

Concurrently, the latent safety problems associated with using large doses of ovulation stimulants to obtain more eggs for IVF cannot be ignored [2]. Furthermore, IVF is an expensive procedure. Repeated cycles place a heavy financial burden on patients and their families. Therefore, it is important to maximize the efficiency of the procedure. Many patients have turned to complementary and alternative medical (CAM) treatments to increase the success rate of IVF. Among these CAM treatments, acupuncture is a frequently used adjunctive therapy.

Since the first report by Stener-Victorin *et al*. in 1999 [3] suggesting that acupuncture can increase the IVF clinical pregnancy rate (CPR), application of acupuncture to IVF has attracted considerable interest from the international community. In recent years, there have been a total of 23 randomized controlled trials (RCTs) evaluating acupuncture in IVF [3-25]. The latest comprehensive meta-analysis [26] of these trials demonstrated the following:

1. Acupuncture improved CPR among women undergoing IVF (Acu. versus Con.:39.5% versus 37.2%, OR = 1.21, 95% CI = (1.00, 1.46)).

2. The difference was more distinct when the types of controls and/or different acupuncture times were examined in a sensitivity analysis. Acupuncture at approximately the same time as COH is more suitable than when performed only concurrently with oocyte aspiration (OA) or embryo transfer (ET) (COH: Acu. versus Con., 31.5% versus 21.2%, OR = 1.75, 95% CI = (1.13, 2.71)).

3. Increasing stimulation intensity at the acupoint surface (as occurred in the Streitberger group), such as transcutaneous electro-stimulation, might induce the same or better therapeutic effects.

The results indicated that more positive effects from acupuncture during IVF can be expected if treatment times are appropriate, the treatment course is enough (at least four sessions), the means of intervention is improved, and syndrome differentiation and treatment according to individual characteristics is emphasized in future programs.

Transcutaneous electrical acupoint stimulation (TEAS) is a combination of transcutaneous electrical stimulation from the West and acupoints from traditional Chinese medicine, which is a method of inputting low frequency-pulse current into the body via the skin to treat diseases such as pain. Real acupuncture is often accompanied by some degree of discomfort or pain, and a portion of patients are afraid of acupuncture. However, this shortcoming of real acupuncture can be avoided by non-invasive stimulation (TEAS), and patients may find it more acceptable, both physically and mentally. Therefore, TEAS may have a more positive therapeutic effect. Zhang R demonstrated the positive effects of TEAS in women undergoing IVF [26], but there were no comparisons between TEAS and electro-acupuncture (EA).

Thus, the primary purpose of this study is to explore whether there are any differences between EA and TEAS in increasing pregnancy rates in women undergoing IVF compared with conventional IVF.

## Methods/Design

This study is designed as a multicenter, randomized, parallel-controlled, assessor- and statistician-blinded trial. Participants will be included from the following five hospitals: Affiliated Tongji Hospital, Union Hospital of Huazhong University of Science and Technology, Wuhan General Hospital of Guangzhou Military Command, Hubei Maternity and Child Care Hospital, and Renmin Hospital of Wuhan University. Each research center must be in strict accordance with the inclusion and exclusion criteria. The study will be conducted in the following sequence: patients will be enrolled after screening via the eligibility criteria, they will be randomized, they will undergo an approximate two-week treatment period, they will undergo a 40-week follow-up period, and assessment will follow. The research protocol has been approved by the Clinical Trial Ethics Committee of Tongji Medical College, Huazhong University of Science and Technology (approval number: (2012) (110)-1) and registered on the ClinicalTrials.gov Protocol Registration System (https://register.clinicaltrials.gov, ClinicalTrials.govID: NCT01608048). Written informed consent will be obtained from each participant. Patients will be recruited to join the study only once and will not receive any monetary compensation for study participation.

### Eligibility criteria

Women presenting to the reproductive medicine center of the involved hospitals will be screened for fitness to undergo IVF. All of the women with an indication for IVF, such as tubal infertility, severe male factor infertility, severe endometriosis, unexplained infertility, immune infertility, and anovulatory infertility, will be informed of the study.

The inclusion criteria are the following: (1) infertile women <40 years of age undergoing a fresh IVF or intracytoplasmic sperm injection (ICSI) cycle; (2) who have a potentially lower success rate, which is defined as two or more previous unsuccessful ETs (fresh or frozen); (3) who are willing to sign an informed consent form indicating that they are aware of the investigational nature of this study, which is in keeping with the institutional policies; and (4) who are willing to return to the study site for visits. The inclusion criteria were necessary because women who have experienced several unsuccessful OAs or ETs may easily accept randomization into this study, and adding TEAS or EA may significantly improve their clinical outcomes.

The exclusion criteria are the following: (1) have major medical illnesses (such as stage III heart disease, severe hypertension, uncontrolled diabetes mellitus, positive HIV status, severe bleeding dyscrasias, *etcetera*) possibly precluding IVF or pregnancy; (2) have FSH levels greater than 20 IU/L; (3) have received donor eggs; (4) have cutaneous lesions within the acupoint area; and (5) had previously participated in this study or previously undergone acupuncture (in whatever modality) as infertility treatment.

The withdrawal criteria are the following: (1) a patient is deemed unfit for the inclusion criteria; (2) early discontinuation for any reason (for example, consent withdrawal, adverse events, and treatment failure); (3) the patient does not strictly abide by the intervention protocol or uses other methods beyond the project that may affect pregnancy outcome; and (4) complete data missing for primary outcomes.

Patients have the right to decline participation in the study, and they may withdraw their consent at any time. Their consent or refusal to consent will not affect their expected IVF intervention.

### Sample size

Sample size calculation is based on the increased range of CPR from acupuncture as described in previous studies (13% to 18% based on the following studies: Stener-Victorin, 17.6% [3]; Paulus, 16.2% [4]; Westergaard, 16% [7]; Dieterle, 18% [8]; and Sator-Katzenschlager, 13.5% [25]). Smith CA chose a conservative 7% estimate based on their previous study [27]. The increased range of clinical effects from TEAS compared with the control group was 13.4% to 20.7% [28]. Therefore, we estimated a 7% increase for the EA group and a 15% increase for the TEAS group compared with the control group. The possible proportion of women with a clinical pregnancy for women with two or more cycle failures in the control group was 20% [27]. To detect differences using a pairwise comparison method, the sample size should be 1,850 according to optimum allocation (700 for the TEAS group, 700 for the EA group, and 450 for the control group) using the Shieh-O'Brien approximation method assuming that alpha (two-sided) is 0.05, the overall power is 0.90, the power between the TEAS and EA groups is 0.80, and the power between the EA and control group is also 0.80. A total sample size of 2,220 women (840 for the TEAS group, 840 for the EA group, and 540 for the control group) is required allowing for a 20% loss due to canceled cycles or no ET.

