### Randomization and blinding

Included patients will be randomly divided into three groups: the TEAS group (conventional IVF + TEAS), the EA group (conventional IVF + EA), and the control group (only conventional IVF).

Fundamental characteristics of randomization include the inability of researchers to predict a patient’s assignment and no assignment changes after randomization. The randomization sequence will be generated by a computerized random number generator using the simple-randomization method (Excel, Microsoft Office 2007). A ‘patient’ database, which lists basic information such as patient name and contact details and a ‘randomization’ database, which contains data on patients who were registered in the trial, along with their allocations, will be generated. The ‘patients’ database is accessible to any researcher, whereas the ‘randomization’ database is password-protected; thus, it will be accessible only by the principal investigator and a nominated computer technician. Immediately before intervention, the acupuncturists will access the ‘patients’ database, type in the patient’s name and details, and hit an icon to randomize the patient. This act will lead to a dialog box asking the researcher to confirm that the patient is eligible. After the ‘okay’ button is pressed, patient information is automatically sent to the randomization database, where randomization takes place [29]. Grouping information will subsequently be sent to the acupuncturists for TEAS or EA treatments.

The assessor will assess the treatment outcome. The assessor will not be the acupuncture practitioner and will be blinded to the allocation results until the end of the study. The statistician will also be blinded to the concrete allocation until after the statistical analysis. The procedure will be performed with blinded staff as much as possible; however, the patients and the acupuncturists will not be blinded because the control group did not obtain sham TEAS or sham acupuncture.

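### The 700/700/450 split gives about 78–79% power for EA versus control and 90% for TEAS versus EA, not the stated 80% and 80%, so *optimum* and the overall 0.90 need restating

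*Protocol article*

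**What the plan says.** All the inputs are in the Sample size section of the protocol article. The control rate is given as clinical pregnancy in women "with two or more cycle failures in the control group was 20"%. For the active arms, "we estimated a 7% increase for the EA group and a 15% increase for the TEAS group compared with the control group". The calculation is pairwise, by a named approximation, "assuming that alpha (two-sided) is 0.05". Three power figures follow. The first is a global one: "the overall power is 0.90". The second concerns the two active arms: "the power between the TEAS and EA groups is 0.80". The third concerns the contrast with the smallest assumed difference: "the power between the EA and control group is also 0.80". The resulting total of 1,850 is split "according to optimum allocation (700 for the TEAS group, 700 for the EA group, and 450 for the control group"), then raised to 2,220 (840/840/540) for a 20% loss from cancelled cycles or no transfer. The article gives no criterion for *optimum*, no definition of overall power and no adjustment for several comparisons. The Statistical analysis section plans chi-square tests on both an intention-to-treat and a per-protocol basis. Women with no primary outcome data count as not pregnant under intention to treat.

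**The concern.** The smallest arm, control, belongs to the contrast with the smallest assumed difference (7 points, against 8 points for TEAS versus EA). The contrast between the two largest arms has the larger difference. If both contrasts are meant to have 80% power, the split favours the one that needs fewer women.

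What is at stake is whether the stated operating characteristics can be relied on. A reader who later meets a non-significant EA versus control result will judge it against a claimed 80%. A reader who takes the overall 0.90 as a joint or three-group power will be misled about what it describes.

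**Working it through.** **Inputs.** From the Sample size section: control 20%, EA 27%, TEAS 35% (increases read as absolute points); two-sided alpha 0.05, unadjusted; arms 700/700/450. From the Statistical analysis section: chi-square test.

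**Formula** (pooled normal approximation, matching the uncorrected chi-square test):

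power = Φ[(|p1 − p2| − 1.96·s0) / s1], where s0 = √[p̄(1 − p̄)(1/n1 + 1/n2)] and s1 = √[p1(1 − p1)/n1 + p2(1 − p2)/n2].

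**The plan's own figures at 700/700/450**

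- EA versus control: p̄ = (450×0.20 + 700×0.27)/1,150 = 0.2426; s0 = 0.02590; s1 = 0.02524. (0.07 − 1.96×0.02590)/0.02524 = 0.762, so power is 77.7%. Stated: 80%.
- TEAS versus EA: p̄ = 0.31; s0 = 0.02472; s1 = 0.02463. (0.08 − 1.96×0.02472)/0.02463 = 1.281, so power is 90.0%. Stated: 80%.
- Three-group chi-square test: about 99.95%. All three pairwise tests significant together: about 69% by simulation. Neither is 90%.

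**Sensitivity to the formula** (two-sided 0.05)

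| Method | EA vs control | TEAS vs EA |
|---|---|---|
| Pooled | 77.7% | 90.0% |
| Likelihood ratio (one reading of the named approximation) | 77.8% | 90.0% |
| Simulated chi-square, 1,000,000 runs | 77.9% | 90.0% |
| Arcsine | 78.2% | 90.0% |
| Unpooled | 79.2% | 90.1% |
| Logit | 76.9% | 89.8% |
| Continuity-corrected | 75.5% | 88.9% |

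Every row is below 80% for EA versus control and about 9 to 10 points above 80% for TEAS versus EA. With 700 in EA, 80% needs 494 controls (pooled) or 467 (unpooled).

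**Is the split optimum for 80%/80%?** A grid search with the pooled formula finds that about 1,604 women (434 TEAS, 650 EA, 520 control) give 80.0% on both contrasts, which is 1,850 − 1,604 = 246 fewer. For a fixed 1,850, the split with the best worst-case power is about 495/765/590, with 85.3% on both. The most women go to EA, the arm shared by both contrasts.

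**After loss.** 2,220 × 0.8 = 1,776, that is 672/672/432 under the planned ratio.

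| Scenario (pooled) | EA vs control | TEAS vs EA |
|---|---|---|
| Planned ratio, 1,850 evaluable | 77.7% | 90.0% |
| Planned ratio, 1,776 evaluable | 76.0% | 88.8% |
| Equal arms, 1,850 evaluable (617/617/616) | 82.7% | 86.0% |
| Equal arms, 1,776 evaluable (592 each) | 81.2% | 84.6% |
| Planned ratio, ITT on 840/840/540 | 73.4% | 86.0% |
| Equal arms, ITT on 740 each | 78.8% | 81.4% |

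The ITT rows assume that 20% are lost in every arm and count as not pregnant, so the rates become 0.8×20% = 16.0%, 0.8×27% = 21.6% and 0.8×35% = 28.0%. With a continuity correction, 592 per arm gives 79.2% for EA versus control.

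**The case against.** The strongest reply has four parts.

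- *The shortfall is marginal.* With round arm sizes, 0.8 points (unpooled) to 2.3 points (pooled) is little, and it depends on the formula. This stands. A reader might infer that the trial is materially underpowered for EA versus control, and the figures do not support that. The firmer evidence is the gap between about 78% and 90%, which appears under every formula.
- *The trial puts TEAS versus EA first.* The Background names the difference between EA and TEAS as the main question, and the Discussion says the controls chiefly supply a reference pregnancy rate. Large active arms fit that priority. This stands too. A reader might infer that 1:1:1 is the correct allocation, but equal arms are not optimum either, and choosing them is a trade-off for the sponsor. It does not rescue the text, which gives both contrasts the same 80%.
- *An adjusted alpha may lie behind 700.* At 0.05/3, 700 versus 700 gives 80.1% for TEAS versus EA. The article states no adjustment, and EA versus control would then have only 62%, so the stated pair is still not reproduced. If an adjustment was intended, equal arms at 1,850 would miss both targets (74% and 69%).
- *The ratio is not hidden.* The Randomization section says only "Included patients will be randomly divided into three groups". A reader might infer that the allocation ratio is missing. It is not: the arm sizes stand in the Sample size section, and leaving the ratio out elsewhere is ordinary condensation in an article.

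**Conclusion.** The concern holds in a limited form. On the article's own assumptions, 700/700/450 gives about 78–79% for EA versus control by the pooled, likelihood-ratio, arcsine and unpooled formulas, and lower by logit or with a continuity correction. It gives 90% for TEAS versus EA. The overall 0.90 does not describe the three-group test (over 99.9%) or joint significance of all pairs (about 69%); it coincides only with TEAS versus EA, for which 0.80 is stated. The split is not optimum for equal 80% targets, and no other criterion is given.

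This rests on absolute increases, unadjusted two-sided 0.05 and the stated pregnancy rates. It is a misstatement of power and not a demonstration that the design cannot answer its questions. Any restated figure also depends on the analysis set: under intention to treat with lost women counted as not pregnant, the planned split has about 73% and 86%.

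**What to change.** In the Sample size section:

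1. Delete *optimum*, or state the criterion by which the split is optimum.
2. Restate the powers as about 78% (EA versus control) and 90% (TEAS versus EA) at 1,850 evaluable women, and about 76% and 89% after a true 20% loss from 2,220.
3. Say what the 0.90 refers to.
4. Name the analysis set to which each figure applies, and confirm that no multiplicity adjustment was assumed.

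This costs wording only.

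As an option, if the sponsor wants both contrasts at 80% or more without enrolling more women, 740 per arm gives about 81% and 85% among evaluable women after a 20% loss. In an intention-to-treat analysis counting lost women as not pregnant (assumed equal 20% loss per arm) it gives about 79% and 81%, so even this does not secure 80% for EA versus control in both sets. The price is 740 − 540 = 200 more women on IVF alone, about 4 points of TEAS versus EA power, and a changed randomization list. The Trial status section says the trial was still preparing to recruit, so either change could be made before enrolment.

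### The 20% loss allowance was applied as a factor of 1.2, so 2,220 women cover only a 16.7% loss; a 20% loss leaves 1,776, which is 74 short of 1,850

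*Protocol article*

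**What the plan says.** The Sample size section of the protocol article first fixes the number needed for the pairwise comparisons: "the sample size should be 1,850 according to optimum allocation", made up of "700 for the TEAS group, 700 for the EA group, and 450 for the control group". The design conditions are given as "assuming that alpha (two-sided) is 0.05, the overall power is 0.90", with "the power between the TEAS and EA groups is 0.80, and the power between the EA and control group is also 0.80". The planning rates are a 20% clinical pregnancy rate in the control group, 7 points more with EA (27%) and 15 points more with TEAS (35%).

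The section then moves to the number to enrol: "A total sample size of 2,220 women (840 for the TEAS group, 840 for the EA group, and 540 for the control group"), and says that this total "is required allowing for a 20% loss due to canceled cycles or no ET". The abstract repeats the total as the number needed: "A total sample size of 2,220 women is required to detect differences in CPR among the three groups".

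The Statistical analysis section names two analysis sets: intention to treat, with everyone randomized, and per protocol, with withdrawals removed. A woman whose primary outcome data are wholly missing counts as not pregnant in the first and is dropped from the second. The article gives no other loss rate and no inflation formula.

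**The concern.** Canceled cycles and absent transfers happen after randomization, so a 20% loss is a fraction of the women enrolled. To keep a target number after such a loss, the target is divided by 0.8. The printed figures look as if the target was multiplied by 1.2 instead, and that does not return the target once the loss occurs.

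What is at stake is whether the enrolment figure, stated twice as the number required, delivers the 1,850 women on which the stated pairwise power rests. If it does not, the number of women reaching transfer will be lower than planned even when the loss rate is exactly as assumed.

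**Working it through.** **Inputs, all from the Sample size section.** Base requirement 700/700/450, total 1,850. Loss 20%. Enrolment 840/840/540, total 2,220. Two-sided alpha 0.05. Planning rates 35% (TEAS), 27% (EA), 20% (control).

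**Step 1: reproduce the printed figures.** Multiplying by 1.2:
- 700 × 1.2 = 840
- 450 × 1.2 = 540
- 1,850 × 1.2 = 2,220

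The total and every arm match exactly, so rounding plays no part.

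**Step 2: apply the stated loss to the printed figures.**
- 840 × 0.8 = 672
- 540 × 0.8 = 432
- 2,220 × 0.8 = 1,776

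Shortfall: 1,850 − 1,776 = 74, and 74/1,850 = 4.0%.

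**Step 3: the loss that 2,220 does cover.** 1 − 1,850/2,220 = 16.7%.

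**Step 4: the number that a 20% loss implies.** n/(1 − 0.20):
- 700/0.8 = 875
- 450/0.8 = 562.5, rounded up to 563
- 1,850/0.8 = 2,312.5, rounded up to 2,313

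This is 2,313 − 2,220 = 93 more women than printed.

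**Step 5: the effect on power in the set after losses.** For rates p1 and p2 in arms of size n1 and n2, let d = |p1 − p2|, let p be the weighted mean rate, and let
- S0 = √[p(1 − p)(1/n1 + 1/n2)]
- S1 = √[p1(1 − p1)/n1 + p2(1 − p2)/n2]

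Power with pooled variance is Φ((d − 1.96 × S0)/S1). Power with unpooled variance is Φ(d/S1 − 1.96).

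EA versus control (d = 0.07):
- 700 and 450: p = 0.2426, S0 = 0.0259, S1 = 0.0252. Pooled 77.7%, unpooled 79.2%.
- 672 and 432: p = 0.2426, S0 = 0.0264, S1 = 0.0258. Pooled 76.0%, unpooled 77.6%.

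TEAS versus EA (d = 0.08), pooled:
- 700 per arm: 90.0%.
- 672 per arm: 88.8%.

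| Comparison | At 1,850 | At 1,776 | Change | Stated |
|---|---|---|---|---|
| EA versus control, pooled | 77.7% | 76.0% | −1.7 points | 80% |
| EA versus control, unpooled | 79.2% | 77.6% | about −1.6 points | 80% |
| TEAS versus EA, pooled | 90.0% | 88.8% | −1.2 points | 80% |

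The pooled gap to 80% for EA versus control is 80 − 76.0 = 4.0 points. Of this, 80 − 77.7 = 2.3 points are already there at 700 and 450, before any loss, and 1.7 points come from the inflation.

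**The case against.** **20% may simply have been added.** The figures were plainly produced that way, but the sentence describes a loss. A loss comes out of the women enrolled, and no other part of the article redefines it. This reading explains the slip without removing it.

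**Intention to treat keeps all 2,220 women.** This stands as a limit on the point. The 74-woman shortfall concerns the set left after canceled cycles and absent transfers, not the intention-to-treat count. It does not make the sentence right, because women without a transfer would add non-pregnancies and dilute the rates. As an illustration, assume that the planning rates are per woman reaching transfer and that 20% of each arm count as not pregnant. The rates become 0.8 × 35 = 28%, 0.8 × 27 = 21.6% and 0.8 × 20 = 16%, and EA versus control at 840 and 540 has about 73% power pooled, or 75% unpooled. The article does not say whether its rates are per transfer or per woman randomized, so this stays an assumption.

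**The slip is minor.** This also stands. A 20% loss is a round planning figure, the printed total already absorbs 16.7%, and no test, analysis set or estimand changes.

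A reader might infer three stronger things that the article does not support:
- *That the slip costs four points of power for EA versus control, from 80% to 76%.* It costs about 1.7; the rest depends on the base calculation or on the choice of variance formula.
- *That the 1,850 and its stated power are wrong because of this slip.* They come before the inflation and are untouched by it.
- *That enrolling 2,313 would secure 80% for EA versus control.* It would return 700 and 450 after losses, hence 77.7% by the same pooled formula.

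**Conclusion.** The point holds as a minor arithmetic error. The enrolment total and the loss rate attached to it do not agree: 2,220 goes with a 16.7% loss, and a 20% loss goes with 2,313. If 20% are lost, 1,776 women remain, 74 (4%) fewer than the plan's own requirement.

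The cost in power is one to two points in the set after losses. TEAS versus EA stays well above its stated 80%. EA versus control moves a little further below its stated 80% under either variance formula, but with pooled variance most of that gap exists without this error.

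The arithmetic rests only on the printed numbers and on reading the loss as a fraction of the women enrolled. The power figures also assume the planning rates, an equal 20% loss in each arm, and a plain two-proportion test at two-sided 0.05. They are a check on size and do not re-create the Shieh-O'Brien calculation that the article cites.

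**What to change.** Correct one sentence in the Sample size section, in one of two ways:

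1. Keep 2,220 (840/840/540) and state that it allows for a loss of 16.7%.
2. Keep 2,220 and the 20% loss, state that 1,776 women (672/672/432) are then expected to reach transfer, and disclose the slightly lower power for EA versus control: about 76% pooled or 78% unpooled at the planning rates.

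In either case, say that the figure after losses describes women reaching transfer and that the intention-to-treat set remains 2,220.

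The cost is a wording change, with a slightly less favourable power figure under the second option. The total in the abstract can stay. Neither option needs extra women or a change of allocation. Restating the total as 2,313 (875/875/563) would also make the numbers agree, but it means 93 more women to recover 1 to 2 points of power, and this correction does not require it.

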### Statistical analysis

Baseline subject characteristics are described by descriptive analysis, and the balance among groups or subgroups was assessed by analysis of variance or *χ*^2^-test. To assess effects of TEAS and EA, the *χ*^2^-test will be applied to compare frequencies between groups such as the CPR and LBR, and analysis of variance will be performed to compare continuous parameters (gonadotropin dose for example) between the groups (*α* = 0.05). All of the analyses will be based on both an intention-to-treat analysis (ITT, with all randomized patients) and a treated-per-protocol analysis (TPP, with all randomized patients minus withdrawals). Missing patient data for those that dropped out of the study will be analyzed using the last observation carried forward method. Patients with complete data missing for primary outcomes will be considered as a negative ITT pregnancy result and eliminated in the TPP analysis.

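### The 20% allowance for cycles without transfer does not fit the ITT analysis; if the planning rates are per transfer, EA-control power is about 0.73-0.75, not 0.80

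*Protocol article*

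**What the plan says.** All references are to the protocol article.

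- **Sample size, rates.** The control rate is given as "The possible proportion of women with a clinical pregnancy for women with two or more cycle failures in the control group was 20" per cent. For the active arms, "we estimated a 7% increase for the EA group and a 15% increase for the TEAS group compared with the control group". The planning rates are therefore 20% (control), 27% (EA) and 35% (TEAS). No denominator is stated.
- **Sample size, error rates.** The calculation is made "assuming that alpha (two-sided) is 0.05, the overall power is 0.90". Pairwise power is stated separately for two contrasts: 0.80 for TEAS against EA, and the same value for EA against control.
- **Sample size, numbers.** The calculation gives 1,850 women (TEAS 700, EA 700, control 450). This becomes 2,220 (840, 840, 540), "allowing for a 20% loss due to canceled cycles or no ET".
- **Statistical analysis.** Two analyses are planned: an "intention-to-treat analysis (ITT, with all randomized patients"), and a per-protocol analysis (TPP) that drops withdrawals. Neither is named as primary. Comparisons of rates use the chi-square test.
- **Outcome measures.** Clinical pregnancy is confirmed by ultrasound at a fixed interval after embryo transfer (ET).

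**The concern.** The sample size treats a woman with a cancelled cycle or no transfer as lost, and enrols another to replace her. The ITT analysis does not lose her. Because the outcome is defined by a scan after transfer, she stays in the denominator as a non-pregnancy.

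Extra enrolment makes up for lost precision, but not for a smaller difference between arms. If the planning rates describe women who reach transfer, the ITT differences are smaller than the ones the trial was sized on.

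EA against control is the weakest planned contrast. If its real power is below the stated figure, a null result there could be read as stronger evidence of no effect than the design supports.

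**Working it through.** **Inputs.** Rates of 20%, 27% and 35%, two-sided alpha 0.05, and 700/700/450 or 840/840/540 (TEAS/EA/control), all from Sample size. One assumption is added: the same no-transfer share d in every arm. It is set to 20% to match the allowance, then varied.

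**Formulas.** With difference D, s0 = √[p̄(1−p̄)(1/n1+1/n2)] and s1 = √[p1(1−p1)/n1 + p2(1−p2)/n2]:
- pooled power = Φ[(D − 1.96·s0)/s1]
- unpooled power = Φ[D/s1 − 1.96]

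**Step 1: the plan's own figures, 700/700/450.**
- EA-control: D = 0.07, p̄ = 0.2426, s0 = 0.02590, s1 = 0.02524. Pooled power is Φ(0.762) = 0.777; unpooled is Φ(0.813) = 0.792. A likelihood-ratio noncentral chi-square of the Shieh-O'Brien type gives 0.778. The stated 0.80 is reproduced only approximately, and from below.
- TEAS-EA: D = 0.08, power 0.90 by either formula, above the stated 0.80.

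**Step 2: the inflation.** 1,850 × 1.2 = 2,220. Losing 20% of 2,220 leaves 1,776 (672/672/432), not 1,850.

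**Step 3: ITT if the rates are per transfer, d = 20%.** Each rate is multiplied by 0.8: 16%, 21.6% and 28%. D falls from 7 to 5.6 points (EA-control) and from 8 to 6.4 points (TEAS-EA).
- EA-control, 840 v 540: p̄ = 0.1941, s0 = 0.02181, s1 = 0.02122. Pooled power is Φ(0.624) = 0.734; unpooled is Φ(0.679) = 0.751. Simulation with 400,000 runs gives 0.736.
- TEAS-EA, 840 v 840: 0.860 pooled, 0.861 unpooled.

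**Step 4: all readings side by side.**

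| Setting | EA-control (pooled / unpooled) | TEAS-EA (pooled) |
|---|---|---|
| As planned, 700/700/450 | 0.777 / 0.792 | 0.900 |
| ITT, 840/840/540, rates per randomised woman | 0.848 / 0.860 | 0.944 |
| ITT, rates per transfer, 10% no ET | 0.796 / 0.810 | 0.909 |
| ITT, rates per transfer, 20% no ET | 0.734 / 0.751 | 0.860 |
| ITT, rates per transfer, 25% no ET | 0.699 / 0.718 | 0.830 |
| TPP after 20% loss, 672/672/432 | 0.760 / 0.776 | 0.888 |

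**Step 5: is this only the inflation arithmetic?** Dividing by 0.8 instead gives 875/875/563. Under ITT with d = 20%, EA-control power is then 0.751 pooled and 0.768 unpooled, still below 0.80. The denominator is a separate problem from the multiplier.

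**Step 6: how much is dilution?** From the planned 700/450, EA-control falls from 0.777 to 0.734 (pooled) or from 0.792 to 0.751 (unpooled), about 4 points. Against 840/540 with no dilution, the fall is from 0.848 to 0.734, about 11 points.

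**The case against.** **The per-transfer premise is inferred.** Sample size speaks of a proportion of women and cites a source that is not at hand. On a per-woman reading nothing shrinks and both comparisons exceed 0.80. This stands, so the shortfall is conditional. In favour of the per-transfer reading, an allowance specifically for no transfer makes sense only if the rates exclude such women. On the per-woman reading the allowance serves no purpose in ITT. Either way the two sections do not match.

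**The allowance may be meant for TPP.** The withdrawal criteria include early discontinuation for any reason, which could cover cancelled cycles, and no primary set is named. This is fair, but TPP does not rescue the figure: after a 20% loss EA-control power is 0.76-0.78.

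**The missing-data rule is a different matter.** The article also says "Patients with complete data missing for primary outcomes will be considered as a negative ITT pregnancy result". A woman without transfer has a known negative outcome, not a missing one. The point rests on the ITT definition and the outcome definition, not on this rule.

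**Stronger readings that the article does not support.**
- A reader might infer that the stated 0.80 is missed for both comparisons. At the stated alpha TEAS-EA keeps 0.86. It falls below 0.80 (to 0.74) only with a Bonferroni alpha of 0.05/3, which the article does not state.
- A reader might charge the whole distance from 0.80 to 0.73 to the denominator. Part of it is there before any dilution.

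**Conclusion.** The loss allowance does not fit the ITT analysis, and the denominator of the planning rates is not stated. If those rates are per transfer and 20% of each arm has no transfer, ITT power for EA-control at 840/840/540 is about 0.73-0.75, below the stated 0.80. About 4 points of that gap are dilution; the rest is already in the 0.78-0.79 at 700/450. TEAS-EA, at 0.86, still meets its target. If the rates are per randomised woman, ITT power is 0.85-0.86 and about 0.94, and there is no shortfall.

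The figures assume equal no-transfer shares across arms. Treatment runs during stimulation, so the shares could differ. The mismatch bears on a stated design figure. It does not bias the ITT comparison or invalidate the test.

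**What to change.** 1. In Sample size, state whether 20%, 27% and 35% are per transfer or per randomised woman.
2. In Statistical analysis, name ITT with all randomised women as the primary analysis of clinical pregnancy, and make pregnancy per transfer or TPP secondary.
3. Restate pairwise power at 840/840/540 on the ITT denominator.
   - Rates per transfer with 20% no ET: rates 16%, 21.6% and 28%; EA-control about 0.73-0.75, TEAS-EA 0.86. Add the sensitivity of EA-control to the no-transfer share: 0.80-0.81 at 10% and 0.70-0.72 at 25%.
   - Rates per randomised woman: remove the no-transfer allowance as a justification for ITT and give 0.85-0.86 and about 0.94.
4. If TPP power is quoted, base it on 672/672/432: 0.76-0.78 and 0.89.

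This is rewording of two sections, and the article says that recruitment has not begun. The cost is a less favourable stated EA-control power if the rates are per transfer. Restoring 0.80 for that comparison in ITT at 20% no transfer and the same allocation would take about 2,603 women (633 + 2 × 985, pooled) or 2,503 (609 + 2 × 947, unpooled). That is optional; an honest statement of the power at 2,220 is the minimum.
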